## Abstract

**Background:**

Whether patients with advanced gastric cancer with unresectable synchronous liver metastases require surgical treatment remains a controversial topic among surgeons. Recently, an open-label multicenter, international RCT study show that compared with chemotherapy alone, gastric resection combined with chemotherapy had no survival advantage for advanced gastric cancer with unresectable synchronous liver metastases. A limitation of this study was that gastrectomy for gastric cancers was restricted to D1 lymphadenectomy and no metastatic lesions were removed. Whether D2 gastrectomy plus liver radiofrequency plus postoperative chemotherapy could provide benefits to these patients is worthy of further confirmation by high-level evidence-based medicine.

**Methods/Design:**

This study will investigate the efficacy of D2 gastrectomy plus liver radiofrequency plus postoperative chemotherapy compared to chemotherapy alone in a prospective, multicenter, randomized controlled trial that will enroll 200 patients who have advanced gastric cancer with unresectable synchronous liver metastases. The patients will be randomly divided into two groups: the test group (D2 gastrectomy plus liver radiofrequency plus postoperative chemotherapy, n=100) and the control group (chemotherapy alone, n=100). The patients’ general information, past medical history, laboratory tests, imaging results, surgery details, and chemotherapy details will be recorded and analysed. The overall survival (OS) will be recorded as primary endpoints. Progression-free survival (PFS) and the total incidence of complications will be recorded as secondary endpoints.

**Discussion:**

This study is to establish a multicentre randomized controlled trial to compare the efficacy of D2 gastrectomy plus liver radiofrequency combined with postoperative chemotherapy versus chemotherapy alone.

**Trial Registration:**

Chinese Clinical Trial Registry, Approved No. of ethics committee:ChiECRCT20200331. Registered on 15 November 2020. Registration number:ChiCTR2000039964. The study has received full ethical and institutional approval.

**Advantages and Limitations of this Study:**

This is the first clinical trial that will provide evidence on the efficacy of D2 gastrectomy plus liver radiofrequency combined with chemotherapy versus chemotherapy alone for the treatment of advanced gastric cancer with unresectable synchronous liver metastases. A prospective RCT with 200 patients who have advanced gastric cancer with unresectable synchronous liver metastases.

**Clinical Trial Registration:**

[https://www.chictr.org.cn/], identifier ChiCTR2000039964.

## Background

Gastric cancer (GC) ranks fifth in incidence and third in mortality among all cancers worldwide each year (1). Synchronous liver metastasis occurs in 3%-14% of GC patients and has a very poor prognosis (2, 3). Currently, chemotherapy is recommended as the standard treatment for advanced gastric cancer with unresectable synchronous liver metastasis (GCLM) by Japanese, American, and international guidelines (4, 5). Although the therapeutic effect has been improved to a certain extent due to the continuous improvement in chemotherapy in the past decade, patients with GCLM have a poor prognosis under this treatment (6, 7). Therefore, there is an urgent need for a new therapeutic strategy to improve survival and prognosis in patients with GCLM.

Previous studies (8–10) showed that palliative gastrectomy combined with chemotherapy could improve the survival of patients with GCLM. However, a recent multicenter randomized controlled study (11) published in Lancet Oncology reported that gastrectomy plus chemotherapy did not provide a survival advantage in the treatment of GCLM compared with chemotherapy alone. However, the method of GC surgery in this study was D1 lymphadenectomy in gastrectomy for primary gastric tumors, which was performed in patients who received chemotherapy after gastrectomy. The surgical methods used in our study will be D2 lymphadenectomy in gastrectomy for primary gastric tumors, a more thorough dissection for the possible occurrence of lymph node metastasis in patients with GC.

Most of the current clinical studies are retrospective cohort studies (12, 13), so the current evidence is not sufficient to support a treatment strategy of D2 gastrectomy plus liver radiofrequency plus postoperative chemotherapy for standardized treatment of patients with GCLM. At the same time, there is also a lack of prospective studies on the efficacy of D2 gastrectomy plus liver radiofrequency plus postoperative chemotherapy versus chemotherapy alone for treatment in China. If the results obtained in this study are in line with our expectations, this study will supplement the existing deficiency of treatment regimens for GCLM, which is of great significance for improving the prognosis of patients with GCLM in clinical practice, and even for the development of a new, more feasible and effective standardized treatment strategy for patients with GCLM.

## Methods/Design

This study will be a multicenter RCT in which 200 patients will be enrolled from November 2020 to November 2022. They will be randomly designated to the test group or the control group in a 1:1 distribution ratio. The test flow chart is shown in **Figure 1**.

**Figure 1 f1:**
[figure not shown]
This is the whole flow diagram of the test.

### Main Objective

According to the process shown in **Figure 1**, 200 patients with GCLM will be grouped to explore a comparison of the OS of D2 gastrectomy plus liver radiofrequency plus postoperative chemotherapy versus chemotherapy alone.

### Secondary Objectives

- To compare the PFS of patients in the treatment of D2 gastrectomy plus liver radiofrequency plus postoperative chemotherapy to those treated with chemotherapy alone

- To explore a comparison of the total incidence of complications of D2 gastrectomy plus liver radiofrequency plus postoperative chemotherapy to those of chemotherapy alone

### Patient Recruitment and Characteristics

The recruitment method will be to collect patients during routine procedures who were screened by investigators against the exclusion criteria. The researchers will have them sign the informed consent form. The above procedures conform to the provisions of the Measures for Ethical Review of Biomedical Research Involving Human Beings (Trial), the Declaration of Helsinki v.08 and the International Ethical Guidelines for Biomedical Research Involving Human Beings.

### Inclusion Criteria

Patients will be included when they meet all of the following conditions:

- Patients who are male or female, aged 20 to 75 years;- Patients who were diagnosed histologically with primary gastric adenocarcinoma;- Patients diagnosed with clinical T1–3 disease by laparotomy or laparoscopy (for T1-T3 patients with the node positive, in order to eliminate the inter group differences, they were randomly divided into control group or experimental group according to the clinical nodal status (further subgroup: N0–1 vs N2–3). For patients with para-aortic lymph node metastasis above the coeliac axis or below the inferior mesenteric artery (lymph node 16a1/b2 of maximum diameter ≥1 cm), or both, or T4 patients with the node positive, according to the NCCN diagnosis and treatment guidelines for gastric cancer and the recommendations of our multidisciplinary diagnosis and treatment team, neoadjuvant therapy was first chosen) (11);- Patients who will undergo diagnostic laparoscopic exploration combined with peritoneal lavage cytology to exclude peritoneal disseminated implant metastasis that is not visible to the naked eye (14);- Patients who will be examined for the molecular profile of the tumors (HER2, PDL1, MSI and MMR expression) [patients with HER2-positive advanced gastric cancer were excluded since trastuzumab in combination with chemotherapy has become the standard treatment for these patients (15)];- Patients with distant metastases that were limited to synchronous liver metastases confirmed by both laparotomy and CT scan;- Patients with metastatic liver tumor ranging from 2 to 4 with tumor diameters ranging from 1 cm to 5 cm (11) (In order to avoid the omission of potential liver metastases, we used contrast-enhanced liver ultrasound as one of the means of further screening. Considered that unless data are now available from ongoing trials, ablation for resectable liver metastasis lesions should not be used in radiofrequency of liver resection. We recommend all patients to multidisciplinary tumor boards to determine whether the liver metastasis is actually unresectable);- Patients whose PS (performance status) was from 0 to 1;- Patients who have not previously been treated for gastric cancer other than EMR;- Patients who have not previously received radiation therapy or chemotherapy for any other malignancy;- Patients who have no contraindications to treatment (surgery, radiofrequency ablation, and chemotherapy);- Patients and their families voluntarily participated in the study and signed the informed consent form.

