### Terminating Study Criteria

The terminating study criteria are as follows:

- Patients are unable to undergo surgery for various reasons after enrollment (reasons need to be recorded);- The researchers consider that the patients are not suitable to continue the clinical trial (the reason for withdrawal should be recorded);- Patients with serious complications or unbearable adverse reactions;- Patients request that the trial be terminated;- Patients violated the treatment principles (violation of injection and discharge standards, disobedience to the study chemotherapy arrangement, etc.)

We will terminate the study for individual patients once they meet the termination criteria and their data will not be included in the final analysis. Other patients who meet the criteria for admission but do not meet the criteria for termination will continue to participate in our study.

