### Treatment Protocols

All eligible patients will be randomly divided into a test group or a control group according to a 1:1 distribution ratio. The test group will receive D2 gastrectomy plus liver radiofrequency plus postoperative chemotherapy. In the test group, only open surgery is allowed. The control group will receive chemotherapy alone. The chemotherapy regimens of the two groups are the same (11), S-1 plus cisplatin. S-1 will be given orally 80-120 mg/m² per day for the first 3 weeks of every 5-week cycle. The dose of S-1 will be given according to the patients’ body surface area (less than 1.25 m², 80 mg; 1.25–1.5 m², 100 mg; and greater than 1.5 m², 120 mg). Patients will receive cisplatin 60 mg/m² on Day 8 of every 5-week cycle *via* intravenous infusion. **Table 1** shows the treatments applied in this study. **Table 2** shows the medication and usage in this experiment. Because all enrolled patients are tested for the molecular profile of the tumors, such as HER2, PDL1, MSI and MMR expression, follow up treatment protocols could be adjusted according to the patients’ molecular profile, such as trastuzumab or immunotherapeutic antibody. Accordingly, in the statistical analysis of data, different patients also require conduct subgroup hierarchical analysis according to the molecular detection results of tumors to reduce data error.

**Table 1 T1:** The treatments applied in this study.

	gastrectomy (total gastrectomy, distal or proximal gastrectomy plus D2 lymph node dissection)	liver radiofrequency	chemotherapy (S-1 + cisplatin)
test group	√	√	√
control group	—	—	√

**Table 2 T2:** The medication and usage in this experiment.

Chemotherapy drugs	dose	Timing of the drugs (a total of 35 days/cycle)			
		Day 1-7/cycle	Day 8/cycle	Day 9-21/cycle	Day 22-35/cycle
S-1	80-120 mg/m² (oral)	√	√	√	—
cisplatin	60 mg/m² (intravenous infusion)	—	√	—	—

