### Clinical Data

Clinical data from the patients will be obtained by medical staff and recorded on an online electronic platform (http://www.medresman.org.cn) and in the CRF table. The samples will be coded, and the patients’ identity will be known only by the attending physician. The clinical data will include the following: general patient information, past medical history, past surgical history, laboratory examination results, imaging results, surgery details, PFS and OS. The timing and processing of the above recorded contents will be reflected in the CRF table, and the laboratory examinations will mainly assess preoperative and postoperative routine blood, liver function, tumor markers, and inflammatory indicators. The prognosis of GC with liver metastasis (GCLM) was very poor, with a 5-year survival rate of <10% (17). Patients will be assessed at least monthly from baseline for adverse events *via* verbal interview, physical examination, and blood tests, including a complete blood cell count and assessments of liver and renal function, until disease progression. Abdominal CT and measurements of tumor markers, such as carcinoembryonic antigen, carbohydrate antigen 199, carbohydrate antigen 125, carbohydrate antigen 153 and alpha fetoprotein, were done every 3 months.

A detailed description of the above data is shown in the CRF table. **Table 3** shows the test and data acquisition schedule for this experiment.

**Table 3 T3:** The test and data acquisition schedule for this experiment.

Stage	Pre-operation	Intra-operation	Postoperation					Unplanned follow-up
Follow up period	14-1 days		0-12 month	13-24 month	25-36 month	37-48 month	49-60 month	
Baseline data collected	√	—	—	—	—	—	—	—
Inclusion and exclusion	√	—	—	—	—	—	—	—
Sign informed consent	√	—	—	—	—	—	—	—
Group determination	√	—	—	—	—	—	—	—
Fill in the basic information	√	—	—	—	—	—	—	—
Physical examination	√	—	√	√	√	√	√	—
Imaging examination	√	—	√	√	√	√	√	if necessary
Laboratory examination	√	—	√	√	√	√	√	—
Operation information	—	√	—	—	—	—	—	—
Postoperative pathology	—	√	—	—	—	—	—	if necessary
Safety observation	√	—	√	√	√	√	√	if necessary
Record adverse events	√	—	√	√	√	√	√	if necessary
Other works	√	√	√	√	√	√	√	if necessary

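### The liver-only criterion requires laparotomy, but the only open operation described is the test-arm gastrectomy after allocation, so the text leaves room for one-sided removal of patients with occult spread

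*Protocol article*

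**What the plan says.** All conditions under Inclusion Criteria must be met by every patient. Three of them concern surgical staging, and they are worded differently:

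- T stage: "Patients diagnosed with clinical T1–3 disease by laparotomy or laparoscopy". Either procedure is accepted.
- Peritoneum: "Patients who will undergo diagnostic laparoscopic exploration combined with peritoneal lavage cytology to exclude peritoneal disseminated implant metastasis".
- Extent of distant disease: "Patients with distant metastases that were limited to synchronous liver metastases confirmed by both laparotomy and CT scan". Here laparotomy is named, together with CT, and laparoscopy is not offered as an alternative.

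Table 3 (Clinical Data) ticks the inclusion/exclusion check, consent and the row "Group determination" only in the pre-operation column, 14 to 1 days before; the intra-operation column has a dash for each.

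Under Treatment Protocols, "In the test group, only open surgery is allowed" and "The control group will receive chemotherapy alone". Table 1 shows no gastrectomy and no radiofrequency for controls.

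Exclusion Criteria rule out metastases outside the liver. Terminating Study Criteria list, among other grounds, "Patients are unable to undergo surgery for various reasons after enrollment" and the researchers' view that a patient is not suitable to continue. The same section says that the data of patients so terminated do not enter the final analysis.

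**The concern.** An eligibility test should be applied in the same way to every patient, before allocation is known. Here the liver-only criterion names a procedure that the article describes for one arm only, and there as part of treatment after allocation. If a site takes the open gastrectomy as the confirming step, a test patient in whom other spread is seen no longer meets the inclusion and exclusion criteria, and may also be judged unable to have the planned surgery. The termination rules then offer a way out of the analysis. A control with the same occult disease is never opened, is never found out and remains in the comparison.

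The patients lost in this way would tend to have a poor prognosis. Losing them from one arm would improve that arm's OS and PFS even if surgery did nothing. Under Randomization Procedure, clinicians are not blinded, so the decision to withdraw would be taken by people who know the arm.

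**Working it through.** **Setting the text side by side**

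1. Liver-only disease must be confirmed by laparotomy and CT (Inclusion Criteria), for all patients.
2. Eligibility and allocation both fall in the pre-operation window (Table 3).
3. The one open operation described is the test-arm gastrectomy (Treatment Protocols, Table 1).
4. From 1 to 3: unless controls have a staging laparotomy that the article does not show, they cannot meet the criterion as worded, and test patients meet it only after allocation.
5. Laparoscopy with lavage is required in both arms, so peritoneal spread can be found in both. What remains one-sided is spread that only the later open operation would reveal.
6. Exclusion Criteria and Terminating Study Criteria together would permit withdrawal of such a patient and omission of the data. Neither section names spread found at operation as a ground; this step is an inference.

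**Scale**

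The plan states no figure on this point, so there is nothing to reproduce. The following is an illustration.

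From the document: 200 patients, 100 per arm, primary endpoint OS. Assumed, not in the document: exponential survival with a median of 14 months, censoring uniform between 36 and 60 months, no treatment effect, a fraction *f* of patients with residual hidden spread, a death hazard *h* times that of the others, every hidden case in the test arm found and deleted, and none deleted among controls. The test is the log-rank at one-sided 2.5%. That level is also a choice, since the plan gives α = 0.05 without stating sidedness.

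Expected deletions from the test arm are 100 × *f*: 5, 10 or 20 patients for *f* = 5%, 10% or 20%.

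At time zero the control hazard, relative to a patient without hidden spread, is 1 + *f*(*h* − 1), so the apparent hazard ratio starts at 1 / [1 + *f*(*h* − 1)]:

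- *f* = 5%, *h* = 1.5: 1 / 1.025 = 0.98
- *f* = 10%, *h* = 2: 1 / 1.10 = 0.91
- *f* = 20%, *h* = 3: 1 / 1.40 = 0.71

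It then moves towards 1 as the high-risk controls die, so the average over follow-up needs simulation. With 20,000 trials per setting:

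| Hidden spread *f* | Hazard multiple *h* | Apparent OS HR | False claim for surgery (one-sided) |
|---|---|---|---|
| 5% | 1.5 | 0.98 | 3.0% |
| 5% | 2 | 0.97 | 3.9% |
| 5% | 3 | 0.96 | 4.6% |
| 10% | 1.5 | 0.97 | 4.3% |
| 10% | 2 | 0.95 | 5.5% |
| 10% | 3 | 0.93 | 7.2% |
| 20% | 1.5 | 0.93 | 6.7% |
| 20% | 2 | 0.89 | 10.4% |
| 20% | 3 | 0.86 | 16.1% |

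With nobody removed (*f* = 10%, *h* = 2), the same program gives HR 1.00 and 2.6%, so the excess comes from the removal alone. PFS was not simulated. The direction is the same by the same reasoning, but its size is not estimated here.

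**The case against.** A reader might infer that controls have no staging operation at all, and that the design finds and removes hidden metastases in the test arm only. The article does not support that.

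- The inclusion conditions bind both arms, and they include diagnostic laparoscopy with lavage, CT and contrast-enhanced liver ultrasound. Table 1 lists treatments; its dashes for controls say nothing about staging.
- The pre-operation column in Table 3 is read most naturally as before the therapeutic operation. The table has no row for laparoscopy, lavage or molecular testing either, although all are required, so its silence does not show when staging takes place. The criterion is phrased as something already confirmed at inclusion, and a condensed article may leave the sequence to the full protocol.
- No sentence says that spread found at operation leads to withdrawal.
- The loss of data comes from the termination rule. If all randomised patients were analysed as allocated, the bias computed above would disappear even with the laparotomy wording unchanged.
- The simulation deletes every hidden case, and its prevalence is not derived from what remains after the staging already required.

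All of this stands, and it narrows the point. It does not remove it. The criterion names laparotomy where the T-stage criterion accepts either procedure, so laparoscopy does not satisfy it as written. No laparotomy is described for controls. Repairing the termination rule alone would leave a criterion that controls cannot be shown to meet, and a site could still void a test patient as never having been eligible.

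**Conclusion.** The conflict of wording is in the text. The bias is a route that the text leaves open, not a stated feature of the design. It needs three things: spread missed by laparoscopy, lavage and imaging; a site that treats the operative finding as a failure of eligibility or a bar to surgery; and omission of that patient's data.

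If all three occur throughout, the apparent OS hazard ratio under no effect lies between about 0.98 and 0.86, and the one-sided false-claim rate between about 3% and 16% instead of 2.5%. Prevalence, hazard multiple, median survival and complete removal are assumptions. Because both arms already undergo substantial staging, the lower end is more plausible, and there the distortion is small. The direction is always in favour of surgery, and it falls on the primary endpoint. The change is worth making because it costs little, but the point should be held with moderate confidence.

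**What to change.** Reconcile Inclusion Criteria, Terminating Study Criteria, Treatment Protocols and Table 3 so that they state:

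1. which procedure confirms that metastases are limited to the liver, that it is the same in both arms, and that it is complete before the randomisation envelope is opened (the choice of procedure is for the trial team);
2. that findings at the test-arm operation do not make a randomised patient ineligible;
3. that all randomised patients are analysed for OS and PFS in their allocated arm, whether or not the planned surgery could be carried out.

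The cost is the rewording of one criterion, a clarification of Table 3 and a sentence in the termination section. Provided that the procedure chosen is one already required of everyone, no patient undergoes anything extra. The downside is that test-arm patients with spread found at surgery stay in the analysis and slightly dilute any true effect.

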
### Exclusion Criteria

Patients will be excluded when they meet any of the following conditions:

- Patients with a diagnosis of primary tumors other than gastric cancer;- Patients who have gastric cancer metastases in sites other than the liver;- Patients who have coagulation dysfunction that cannot be corrected;- Patients with viral hepatitis and cirrhosis;- Patients with diabetes mellitus, uncontrolled or controlled with insulin;- Patients treated with systemic steroids;- Patients suffering from psychosis;- Patients with heart, lung, liver, brain, kidney or other organ failure;- Patients who have ascites and cachexia preoperatively, and their general conditions are poor;- Patients who refuse to sign the informed consent to take part in this study;- Female patients who are during pregnancy or breast-feeding (except for those women who are breast feeding but consenting to surgery and chemotherapy).

